### Lentil fortification with Fe

Lentils were fortified with Fe at the Saskatchewan Food Industry Development Center Inc. (Food Center) in collaboration with the Department of Plant Sciences of the Crop Development Center (CDC) of The University of Saskatchewan, Canada. A small red lentil variety (CDC Maxim) was used, similarly to the previously developed protocol [19]. In brief, the fortification method was developed to identify the most suitable product types (decorticated unsplit lentil dal), appropriate methods for fortification, dosage and colorimetric changes, and the storability of Fe-fortified lentil dal among three different Fe fortifiers (FeSO_4_·7H_2_O, NaFeEDTA and FeSO_4_·H_2_O). NaFeEDTA was found to be the most suitable Fe fortifier of lentil dal at 1600 μg g^− 1^ (fortifier Fe concentration), providing 13–14 mg more Fe 100^− 1^ g of dal [19]. The fortified lentils were bagged in 20-kg airtight polyvinyl bags and stored at room temperature before being shipped to Bangladesh.

### Intervention

There will be three arms in this effectiveness trial. Arm 1 will receive Fe-fortified lentils, arm 2 will receive unfortified lentils, and arm 3 will receive no intervention i.e. no additional lentil (usual intake group) and will serve as a control group. The usual intake group will serve as control for the lentil-related research questions, but not those pertaining to the fortification itself. Participants will not be asked to change anything about their food intake during the study, including lentil intake. Participating adolescents will be served a thick preparation of cooked lentils (37.5 g raw lentil) 5 days per week for 85 feeding days (around 4 months).

A team of 3 will manage the distribution of the lentil preparation: (1) a locally-recruited cook, (2) a research assistant who will measure and serve the cooked lentils, and (3) an Adolescent Club leader who will assist in serving and ensuring that safe drinking water is available. A locally acceptable, standard lentil dal recipe identified during the earlier feasibility study will be used. The recipe for thick cooked lentils will include turmeric 5 g, chopped onion 40 g, garlic 8 g, green chili 3 g, water 700 ml, salt 1.5 teaspoon, soybean oil 10 teaspoons, and one small bay leaf (*tejpata*) per 100 g uncooked lentils. The average cooking time would be around 18 min, and the approximate weight (after cooking of 37.5 g raw lentil) would be approximately 200 g [15]. All adolescent boys and girls who attend the BRAC Adolescent Clubs will be offered the cooked lentils during the period of the intervention; however, the information on those girls not meeting the inclusion criteria will not be analyzed.

### Sample size, randomization and blinding

Considering the lower estimation of the expected difference in mean serum ferritin (sFer) (5 ±20 μg/L) with 80% power at *p* < 0.05 significance level and inter-cluster correlation (ICC) at 0.025, a total of 48 clusters will be selected falling under 16 blocks. Each block will have 3 clubs resulting in a total of 48 clubs. Each club is considered as cluster. Within each cluster, 27 eligible adolescent girls will be selected. Clusters will be randomly assigned to the intervention within each block. In this cluster RCT, units of randomization will be Adolescent Clubs where data will be collected from individual girls. First, a total of 48 clubs will be randomly selected out of 75 clubs. Each cluster will be randomly assigned under 16 blocks. There will be three clusters in each block and three study arms (Fe-fortified lentil, non-Fe-fortified lentil, or usual intake) will be then randomly allocated within blocks using computer-generated random assignments. Equal numbers of clubs (*n* = 16) will be assigned to each arm and there will be equal numbers of participants (*n* = 420) in each arm. Finally, 420 adolescent girls will be included in each arm including an additional 20% to account for loss to follow up. The total sample size including all three arms will be 1260 adolescent girls. For the cognitive testing, a subsample of the intervention group (*n* = 80 adolescent girls in each group, 5 per cluster, a total of *n* = 240 participants) will be selected assuming a two-tailed, 5% type I error rate with 80% power, and an ICC of 0.025. This is based on a recent biofortified iron study with 70% effect size [13, 20]. We further increased the sample size to a total of 360 adolescent girls (e.g., *n* = 120 adolescent girls in each group, considering a 50% attrition rate). We assumed a 20% attrition rate in our first outcome; however, we assume the attrition rate may be higher in the cognitive part as it would take longer, plus many of the participants may have not seen or physically touched a laptop in their lifetime. We assume these will create a greater burden to them resulting in a higher attrition rate. Cluster numbers were sequential at 4-digit point because we wanted to make our UID an 8-digit number: 2 digits for the club ID, 4 digits for cluster, and 2 digits for the participant. This makes the UID more unique and will avoid confusion among the research assistants about each part of the UID. A potential problem with sequential numbering (e.g., 1 .. 16) would be that the different digits used for the participants may lead to different sizes of the UID stickers, and thus to difficulty using the UID stickers during blood sample collection (e.g., on paperwork, blood sample tubes, etc.).

The study will follow the double-blind strategy in distributing the Fe-fortified or non-Fe-fortified lentils to the participants. The double-blind strategy (blinding both of trial participants and outcome assessors) will be carried out by a third party under the direct supervision of the principal investigator of the project. Each lentil packet (stiff cardboard box) will contain double-layered color-coded bags. The outer layer will be marked with an adhesive colored sticker. The inner layer (food-grade bag) will be representing Fe-fortified or non-Fe-fortified lentils. Color-coded packets will be delivered to the intervention Adolescent Clubs. Blinding will be broken within 24 h availability in any instance of unexpected or untoward conditions, for example, mass hysteria, mass diarrhea linked to served lentils, unexpected death, or life-threatening condition of the participants, etc. During the data collection period, the researchers will be in touch with the local research assistants on a daily basis to receive daily updates on the research from the field. If required, an urgent message will be sent by field researchers to all the study investigators if there are any unexpected or untoward conditions. All the Institutional Review Boards (IRBs) will be informed if such a situation occurs.

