### Study settings and target population

The effectiveness study will be conducted at the BRAC Adolescent Clubs [16]. These clubs target all adolescent boys and girls in the community, regardless of their school attendance, marital status, or socio-economic status. The clubs provide a unique opportunity for adolescents to socialize in both rural and urban settings. Each club has a membership of 25–40 adolescent boys and girls aged 10–19 years. The clubs operate in the afternoons in BRAC school environments. In the absence of such facilities, a room is rented locally by BRAC. The clubs have various activities to encourage the participation of adolescent girls and boys such as life-skill-based education (LSBE) sessions, access to mini-library facilities, cultural activities, and sports. BRAC provides all materials related to these activities, e.g., books, magazines, and games equipment. The clubs will be selected from four subdistricts (*Upazilas*) i.e., Muktagacha, Nanadail or Mymensingh Sadar (Central), Bhaluka, and Gaffargaon, of the Mymensingh district.

The study has been carefully designed to ensure that all of the adolescent girls between the ages of 10–17 years meet the study inclusion criteria: non-smoking, not married, not pregnant, not breastfeeding, and generally healthy. Adolescent girls who choose not to participate, are ill during recruitment, or are known to have infectious disease will be excluded. Standard Protocol Items: Recommendations for Intervention Trials (SPIRIT) 2013 (Fig. 1) will be used to report the study [17]. Table 1 presents a summary of the trial according to the World Health Organization (WHO) Trial Registration Minimal Data Set as described by Moja et al. [18].

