### Statistical analysis

Baseline characteristics, i.e., all covariates, will be examined for group comparability to determine if randomization was successful. An intent-to-treat approach will be followed in the analyses of outcome data at the end of the intervention. Outcome variables such as sFer, and Hb will be set using different cutoffs from the National Micronutrients Status Survey 2011–12 [2]. Data will be analyzed with and without adjustment for baseline characteristics. Group means for changes in biochemical variables, anthropometric measures, and post-intervention morbidity rates will be compared using mixed models (with cluster as the random effect), with the respective baseline values serving as the primary covariate. After these preliminary analyses, key outcome variables (sFer and the cognitive performance of the adolescent girls) will be re-examined and additional covariates will be included in the model such as factors that differed by intervention arm, i.e., age, socio-economics, anthropometrics, food security, drinking safe water, hygiene practices etc.). Additional continuous outcome variables will also be examined using a generalized linear model (GLM), adjusted for confounding factors such as age, socio-economics, anthropometrics, food security, drinking safe water, hygiene practices, etc. Categorical variables will be compared using the chi-square test or logistic regression adjusted for possible confounding factors. With the assumption that data will be missing at random (MAR), multiple imputation or likelihood-based mixed models will be used for analysis, after complete case analysis and examination of missing data within and between treatment groups. All outcome variables will be examined for normality, and outliers will be identified. Data collected from adolescent girls suffering from severe Fe deficiency and/or acute infection will participate in all aspects of the study but results of supplementation in this group will be analyzed separately. All analyses will be performed using SPSS for Windows PAWS version 25. A *p* value <0.05 will be considered statistically significant for all main effects.

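### Forming the 16 blocks of clubs at random secures equal arm sizes but no balance on subdistrict; the block-free model is valid, but a cheap gain in balance and precision is forgone

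*Protocol article*

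**What the plan says.** The section on sample size, randomization and blinding draws 48 of 75 clubs at random. On the blocks it says "Each cluster will be randomly assigned under 16 blocks", and "Each block will have 3 clubs resulting in a total of 48 clubs". The three arms are then allocated within each block by computer. No factor that would make the clubs of a block alike is named.

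The section on study settings gives one natural candidate: "The clubs will be selected from four subdistricts". It is not used in the allocation.

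In the section on statistical analysis, changes in the outcomes are "compared using mixed models (with cluster as the random effect), with the respective baseline values serving as the primary covariate". Block is not in that model. Neither block nor subdistrict appears among the further covariates listed, although that list is open-ended.

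**The concern.** Blocking helps when clubs within a block resemble each other on something that predicts the outcome. Randomising within such blocks spreads that factor evenly over the arms and removes its variance from the comparison. Triplets formed by chance do neither. They only fix the number of clubs per arm, which plain restricted allocation would also do.

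With 16 clubs per arm, chance differences between arms in their mix of subdistricts can be sizeable. The study design section gives avoidance of confounding and baseline representativeness as a reason for the design, and random triplets add nothing to that beyond ordinary randomisation. At stake are face validity of the primary comparison (fortified against unfortified lentils) and some precision.

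**Working it through.** **Inputs**
- Difference 5 and SD 20 μg/L: "expected difference in mean serum ferritin (sFer) (5 ±20 μg/L) with 80% power at" (the ± is read as the SD).
- ICC and blocks: "inter-cluster correlation (ICC) at 0.025, a total of 48 clusters will be selected falling under 16 blocks". On a total variance of 400, the between-club variance is 0.025 × 400 = 10 and the within-club variance is 390.
- Significance: p "value <0.05 will be considered statistically significant for all main effects". Two-sided testing is assumed for ferritin; it is stated only for cognition.
- Girls per arm: 420, said to include 20% for loss. 420 × 0.8 = 336, and 336/16 = 21 analysed per club.
- Not in the documents: the share f of between-club variance that informative blocks would explain (assumed 30–50%) and the number of clubs per subdistrict (assumed 48/4 = 12).

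**The plan's own figure.** Two means with these inputs need 252 girls per arm. With 27 per club the design effect is 1 + 26 × 0.025 = 1.65, and 252 × 1.65 = 416. That matches 420 only with no allowance for loss. This is a separate matter; here it only explains why the starting power below is under 80%.

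**Step 1: design as written (f = 0).** Variance of an arm difference = (2/16) × [10 + 390/21] = 0.125 × 28.57 = 3.571, so SE = 1.890. Error df without block = 48 − 3 = 45. With block, df = (16 − 1) × (3 − 1) = 30.
- In 100,000 simulated trials the block-free model covers 95.0%. It is the right model for random blocks.
- Power from the noncentral t is 73.5% on 45 df and 72.6% on 30 df (simulated: 73.7% and 72.7%). Adding block to random triplets therefore costs about one point and gains nothing.

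**Step 2: informative blocks, fitted in the model.** Variance = 0.125 × [10(1 − f) + 390/21], with 30 df.

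| f | variance | SE | power |
|---|---|---|---|
| 0 | 3.571 | 1.890 | 72.6% |
| 0.3 | 3.196 | 1.788 | 77.2% |
| 0.5 | 2.946 | 1.717 | 80.5% |

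**Step 3: informative blocks, left out of the model.** The model SE stays at 1.890 while the true SE falls. The ratio is 1.890/1.788 = 1.057 at f = 0.3 and 1.890/1.717 = 1.101 at f = 0.5. The t critical value on 45 df is 2.014. Scaled by these ratios it becomes 2.129 and 2.217, and the two-sided tail areas of t on 45 df are 3.9% and 3.2%. Simulation agrees (3.9% and 3.2%). Intervals would be too wide, not too narrow.

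**Step 4: balance.** With 12 clubs per subdistrict and random allocation of 16 clubs to each arm (200,000 allocations), the two lentil arms differ by three or more clubs in at least one subdistrict in about 71% of allocations, and by four or more in about 44%. With triplets formed within subdistrict each difference is zero.

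**The case against.** The strongest reply is that the written randomisation and the written model fit each other. Blocks formed at random carry no variance in expectation, so leaving them out is correct, and adding them to the present design would lose a little power. That stands in full.

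A reader might infer that a blocked trial analysed without block must give wrong intervals. The documents do not support this. The distortion in step 3 needs informative blocks, which the article does not describe, and even then it is conservative.

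A reader might also infer that three blood samples per girl, with no girl-level random effect, mean that repeated values are treated as independent. The analysis section compares changes at the end of the intervention with the baseline value as covariate. The Discussion mentions differences at midline, but no model pooling midline and endline is specified, so this does not follow either.

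Three further replies stand in part:
- Chance imbalance in subdistrict does not bias a randomised comparison, and the planned adjustment for factors that differ by arm answers some of it. Adjustment chosen after seeing the imbalance is still a weaker protection than balance by design.
- The 30–50% is an assumption. Between-club variance is only 2.5% of the total, and baseline adjustment should reduce it further, so the gain in step 2 is probably near the upper end.
- The article does not give the number of clubs per subdistrict and leaves one of the four areas open between two names, so exact triplets within every subdistrict may not be possible.

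**Conclusion.** The point holds as a missed improvement, not as an error of inference. The random triplets secure 16 clubs per arm and no prognostic balance, and the club-level mixed model without block is valid for them.

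The balance forgone is substantial if clubs are spread about evenly over the subdistricts (about 71% of allocations with a difference of three or more clubs somewhere). The precision forgone is modest: power of about 77–80% instead of about 73%, if blocks explain 30–50% of between-club variance, 21 girls per club are analysed, and the ICC is 0.025 before any baseline adjustment. If subdistrict predicts little, there is no gain in power, and fitting block costs about one point.

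The two parts of the remedy belong together. Informative blocks that are then left out of the model would give intervals that are too wide, with a type I error of about 3.2–3.9%.

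**What to change.** Before randomisation:

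1. Form the triplets within subdistrict as far as the number of selected clubs allows. With 12 clubs in each, this is four triplets per subdistrict; clubs left over elsewhere can form a mixed triplet.
2. Randomise the three arms within each triplet, as already planned.
3. Put block in every outcome model, or at least subdistrict.
4. State in the protocol how blocks are formed. If they are meant to stay random, say so and say that block is therefore left out of the model.

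**Cost.** The trial status is given as not yet recruiting, so the change needs a list of clubs by subdistrict and one more model term. Block takes up to 15 error df (45 to 30), about one percentage point of power if blocks are uninformative. Subdistrict alone takes 3 df (45 to 42). If clubs have already been allocated, what remains is to prespecify subdistrict as a covariate, which allows for imbalance in the analysis without preventing it.

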### Study design

This manuscript describes the protocol for a double-blind (both the trial participants and the outcome assessors), community-based, cluster-randomized controlled trial designed to test the effectiveness of consuming Fe-fortified lentils to improve Fe stores and cognitive performance (attention, and memory) in adolescent girls in rural Bangladesh. Given the context of this problem, the cluster-randomized controlled trial allows us to (1) avoid confounding and ensure representativeness at baseline; (2) minimize risk of contamination between treatment arms; and (3) examine the temporal relationship between our intervention and the outcome.

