**Fig. 2 Fig2:**
[figure not shown]
Flow chart for the 85-day iron-fortified lentil feeding trial. Demographics, food frequency questionnaire (FFQ), anthropometrics, blood test, cognitive assessment

First of all, healthy female adolescents aged 10–17 years, who are non-smoking, not pregnant, and not breastfeeding, and willing to participate will be included in the study. Those who give consent will be invited to attend the BRAC Adolescent Clubs and venous blood samples will be collected in a private setting within the club by a 3-person team consisting of (1) a medical technologist, (2) a female research assistant and (3) a male research assistant. BRAC local staff will be present to monitor the entire process. Albendazole (400 mg in tablet form) will be provided so that participants are dewormed at the time of the feeding trial meaning that they are free from parasites, such as roundworm, flukes, and tapeworm infestation. Earlier studies suggest that worm infestation is linked with anemia and deworming reduces anemia among children [31–33].

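### The order of club allocation and enrolment is unclear and reads as allocation first; because the usual-intake arm cannot be masked, enrolment could differ by arm in the comparisons with it

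*Protocol article*

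**What the plan says.** All on the Protocol article.

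- **Order, first mention** (Sample size, randomization and blinding): "Within each cluster, 27 eligible adolescent girls will be selected". The next sentence assigns clusters to the intervention within blocks.
- **Order, second mention** (same section): 48 of 75 clubs are sampled first, the three arms are then allocated within blocks of three clubs by computer, and the run closes with "Finally, 420 adolescent girls will be included in each arm including an additional 20% to account for loss to follow up".
- **Entry** (Study settings and target population): girls must be generally healthy, a term the article does not define, and those unwell at recruitment or unwilling are excluded. Data collection tools and technique, below Fig. 2, adds willingness as a condition and continues: "Those who give consent will be invited to attend the BRAC Adolescent Clubs and venous blood samples will be collected".
- **Masking** (Sample size, randomization and blinding): "The study will follow the double-blind strategy in distributing the Fe-fortified or non-Fe-fortified lentils to the participants". Under Intervention, arm 3 receives no lentils. The abstract, Study design and Table 1 nevertheless call the whole trial double-blind.
- **Claim for the design** (Study design): cluster randomisation lets the trial "avoid confounding and ensure representativeness at baseline".
- **Comparisons** (Trial objectives; Intervention): fortified versus unfortified lentils is primary and fortified versus usual intake is secondary. Usual intake is also the control for the lentil-related questions.

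**The concern.** In a cluster trial, randomising clubs makes the clubs comparable. The girls analysed are comparable only if they are identified and consented without the arm being able to influence who enters. If a club's arm is known beforehand, a recruiter's judgement of who is healthy enough, or a girl's or family's willingness to accept three rounds of venous sampling, can differ between a club that serves a meal and one that does not.

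At stake are the secondary comparison and every question about lentils as such. The growth objective is one of these: an effect of unfortified lentils on growth can be read only against usual intake. For these contrasts, the statement that the design avoids confounding would depend on a step the article leaves unclear.

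**Working it through.** **1. The two orders side by side.** The first mention puts selection of 27 girls before assignment of clubs, but it sits among the sample-size figures and carries no sequence words. The second carries sequence words for each step: clubs sampled, arms allocated, girls included in each arm. The text below Fig. 2 opens by saying which girls are included, without placing that before or after allocation. Nothing in the text shown says that girls are consented or measured before allocation, or that recruiters are unaware of the arm. Allocation first is the more natural reading, but it is not fixed.

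**2. Who can tell the arms apart.** Arms 1 and 2 both receive cooked lentils from colour-coded packets, so recruiters should not be able to separate them while the code holds. Arm 3 receives no lentils and no packets. Once the allocation is released, no described measure hides that arm from staff, girls or families.

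**3. Room for choice.** Clubs have 25–40 members, boys and girls aged 10–19. The 27 girls aged 10–17 needed per club are 27/40 = 67.5% to 27/25 = 108% of total membership. Two consequences pull in opposite directions:
- a club whose eligible girls are nearly all taken leaves little scope for selection;
- a club that cannot reach 27 would need girls from outside its membership, which widens the scope.

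**4. Size.** The plan gives no figure for differential enrolment, so only a conditional illustration is possible.

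Inputs from the plan: "Considering the lower estimation of the expected difference in mean serum ferritin (sFer) (5 ±20 μg/L", read as difference and SD; "with 80% power at *p* < 0.05 significance level", taken as two-sided; "inter-cluster correlation (ICC) at 0.025"; 16 clubs per arm.

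The plan's own figure first:
- n per arm without clustering = 2 × (1.96 + 0.842)² × 20² / 5² = 251.2, rounded up to 252
- design effect at 27 per club = 1 + 26 × 0.025 = 1.65
- 252 × 1.65 = 415.8, or 416 per arm

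This is close to 420 before any loss. With 20% loss it would be 416/0.8 = 520. That mismatch is a separate matter and does not bear on this point.

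Precision after 20% loss:
- girls per club = (420/16) × 0.8 = 26.25 × 0.8 = 21
- design effect = 1 + 20 × 0.025 = 1.5
- effective n per arm = 16 × 21 / 1.5 = 224
- SE of a difference between arms = 20 × √(2/224) = 1.89 μg/L

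With an enrolment-driven difference b and no true effect, the chance of p < 0.05 is Φ(−1.96 + b/SE) + Φ(−1.96 − b/SE):

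| Assumed b (μg/L) | b/SE | Error rate, unadjusted |
|---|---|---|
| 0 | 0 | 5% |
| 1 | 0.53 | 8% |
| 2 | 1.06 | 18% |
| 3 | 1.59 | 35% |

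The values of b are assumptions. The table applies to an unadjusted comparison. Statistical analysis plans results with and without adjustment, and its mixed models use baseline values as the main covariate, so these rates are not forecasts for the adjusted result.

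**The case against.** The strongest reply is that the order is only inferred. Selection of girls is mentioned before assignment at one point in the section, and the sentence with 420 girls mainly closes the sample-size reckoning. Figs 1 and 2, the supplementary file and the full protocol, where the order might be plain, are not shown. This stands to the extent that allocation first cannot be stated as fact. It does not dispose of the point: the article itself gives two orders, one of them explicitly sequenced, beside an unqualified double-blind label and a no-confounding claim.

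Three further objections stand, and each limits the point:

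- **The meal as a lure.** A reader might infer that girls would consent in order to get a free meal. Under Intervention and Discussion, all who attend a lentil club are offered lentils whether enrolled or not. An existing member therefore gains no lentils by consenting and loses none by refusing. What remains is new joiners, whose recruitment the article does not describe, and judgements of health and willingness in general.
- **An open source list.** A reader might take the invitation to attend the clubs as proof that recruitment reaches beyond members. It can equally describe where blood is drawn.
- **Adjustment.** A reader might suppose that only baseline ferritin is adjusted for. Statistical analysis names the respective baseline value for biochemical and anthropometric outcomes, so growth is adjusted for baseline growth. Cognition is measured at baseline and is to be re-examined with further covariates. This reduces the bias but cannot remove differences in motivation, household need or health that the covariates do not capture.

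**Conclusion.** The point holds in limited form. The article gives two orders for selecting girls and allocating clubs, and its sequenced text reads as allocation before enrolment. If that order is followed, enrolment could differ by arm in the comparisons with usual intake, because that arm is recognisable and entry rests partly on judgement and willingness.

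A reader might infer that the trial's main result is exposed. The documents do not support this: the primary comparison is between two lentil arms behind coded packets, and it is largely spared as long as the code holds. Nor do they support saying that bias is present, or that it amounts to a given share of the planned 5 μg/L difference. The error rates shown rest on assumed differences of 1–3 μg/L, an SD of 20 μg/L, an ICC of 0.025, 21 girls per club and no baseline adjustment.

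The change is still worth making. It is cheap, the article gives the trial status as not yet recruiting, and it protects a named secondary comparison.

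**What to change.** State one order and follow it:

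1. In all three clubs of a block, identify the eligible girls, obtain consent and assent, and complete the baseline round.
2. Only then release that block's allocation to field staff and clubs. The list may be generated earlier if it is held away from them.
3. Do not enrol girls who join a club after release. They may still attend and eat, as the article already provides for others who are not analysed.
4. Restrict the double-blind label to the two lentil arms. Say that for arm 3 the no-confounding claim rests on enrolment before release.

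A random draw from a closed list should not be required where a club has no surplus of eligible girls. With 25–40 members of both sexes it may be impossible. What matters is that the set of girls is fixed before the arm is known.

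The cost is scheduling: lentils can be delivered to a block only after its baseline is complete. No extra girls, visits or measurements are needed. If enrolment has already begun, report for each club the dates of consent, baseline and release of allocation, so that readers can judge the contrasts with usual intake.

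### The 420 girls per arm contain practically no allowance for the 20% loss they are said to include: unadjusted ferritin power after that loss is about 73–75%, not 80%, and the cognitive subsample keeps 60 per arm, not the stated 80

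*Protocol article*

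**What the plan says.** All of this stands in one paragraph of the protocol article, under Sample size, randomization and blinding.

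- **Ferritin inputs.** The calculation uses the "expected difference in mean serum ferritin (sFer) (5 ±20 μg/L") and is done "with 80% power at" the 5% level. It continues: "significance level and inter-cluster correlation (ICC) at 0.025, a total of 48 clusters will be selected falling under 16 blocks". Sidedness is not stated for ferritin.
- **Clusters.** "Equal numbers of clubs (*n* = 16) will be assigned to each arm", and "Within each cluster, 27 eligible adolescent girls will be selected".
- **Size and loss.** "420 adolescent girls will be included in each arm including an additional 20% to account for loss to follow up", for a total of 1260. Later: "We assumed a 20% attrition rate in our first outcome". The number before the allowance is not given.
- **Cognition.** The stated need is 80 girls per arm, 5 per club (two-tailed 5%, 80% power, ICC 0.025), based on an effect size given as 70%. This is then raised to 120 "adolescent girls in each group, considering a 50% attrition rate".

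Table 1 lists both serum ferritin and cognitive performance as the primary outcome.

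**The concern.** The paragraph gives its inputs, its allowance for loss and its totals, and these do not fit together. If 420 enrolled per arm is close to the number that must be evaluable, the 20% is claimed but absent, and the 80% power no longer holds once the expected loss occurs. The Discussion says that a small effect is expected and that numbers must be large enough to detect it. A null ferritin result would then be read against a power that this calculation does not support. For cognition, a target of 80 completers is missed under the attrition rate chosen to protect it. The count per club also disagrees with the count per arm, so it is unclear how many girls are to be enrolled.

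**Working it through.** **Inputs.** Difference 5, SD 20 (the ±20 read as an SD), ICC 0.025, 16 clubs per arm, 27 girls per club, 20% loss, 80% power: all from the sample-size paragraph. Two-sided 5% is an assumption for ferritin, in line with the two-tailed cognitive calculation. The comparison is between two arms, as in Trial objectives.

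**1. Trying to reproduce 420.**
- Without clustering: n = 2 × (1.96 + 0.8416)² × (20/5)² = 251.2 per arm.
- Design effect: DE = 1 + (m − 1) × 0.025. At m = 27, DE = 1.65; at m = 420/16 = 26.25, DE = 1.631.
- Evaluable girls needed: 251.2 × 1.65 = 414, or 251.2 × 1.631 = 410. Solving with 16 clubs fixed gives 403.
- With an allowance for 20% loss this becomes about 484–497 (× 1.2) or 504–518 (÷ 0.8).

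So 420 matches the need with no loss. It does not reproduce as a figure that includes 20%.

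**2. Power after the stated loss.** Power = Φ(0.25 × √(n/(2·DE)) − 1.96). The t version uses 2 × (16 − 1) = 30 df.

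| Completers per arm | Girls per club | DE | Normal | t, 30 df |
|---|---|---|---|---|
| 420 (no loss) | 26.25 | 1.631 | 81.0% | 78.4% |
| 336 (420 × 0.8) | 21 | 1.500 | 75.4% | 72.6% |
| 345.6 (432 × 0.8) | 21.6 | 1.515 | 76.1% | 73.4% |
| 350 (420 ÷ 1.2) | 21.9 | 1.522 | 76.5% | 73.7% |

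For 336: 336/1.5 = 224, and 0.25 × √112 − 1.96 = 0.686, so Φ = 0.754.

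**3. Counts.** 16 × 27 = 432 per arm and 48 × 27 = 1296 in total, against 420 and 1260.

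**4. Cognition.**
- 80 × 1.5 = 120, but 120 × (1 − 0.5) = 60. Keeping 80 after 50% loss would take 80/0.5 = 160.
- 120/16 = 7.5 girls per club.
- If the 70% means 0.7 SD: 2 × 7.849/0.7² = 32.0; times DE(5) = 1.10 gives 35 per arm. The stated 80 does not follow from that effect.
- Power at 0.7 SD with 60 completers (3.75 per club, DE 1.069): 0.7 × √(60/(2 × 1.069)) − 1.96 = 1.75, so 96.0% (94.8% with t on 30 df).

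**5. Effect of baseline adjustment.** Adjusting for baseline multiplies the variance by about 1 − r². No r is given; for 336 completers, assumed values give (normal/t): r = 0.3, 79%/77%; r = 0.4, 82%/80%; r = 0.5, 86%/84%.

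**The case against.** - **The planned analysis is not unadjusted.** Statistical analysis specifies mixed models with the baseline value as primary covariate. With a moderate baseline correlation, 336 completers per arm reach about 80%. This stands as a limit on the harm: a reader might infer that the trial is underpowered for ferritin, and the document does not establish that. It does not rescue the paragraph, which states no correlation.
- **The cause is not a slip of multiplying instead of dividing.** A reader might infer that from 350 × 1.2 = 420. But the document never states 350, and that base would itself need about 382 (251.2 × 1.522). Multiplying rather than dividing is the difference between 350 and 336 completers, about one point of power. Dividing 350 by 0.8 gives 438 enrolled and still only 74–76.5%.
- **The lower figure uses a stricter yardstick.** The protocol does not specify t on 30 df, and on that basis 420 girls with no loss give only 78%. Like for like, the 20% loss costs 5–6 points.
- **Loss may be smaller.** The feasibility study had no drop-outs. At 10% loss (378 per arm) power is about 78% by normal approximation. This affects how serious the point is, but 20% is the protocol's own assumption.
- **A one-sided test.** At 5% one-sided, 27 per club and division by 0.8, the need is 197.8 × 1.65/0.8 = 408, near 420. Nothing in the document states a one-sided test.
- **Cognitive power.** It is tempting to conclude that 60 per arm falls below 80% power. That requires an effect well under 0.7 SD, which the document does not give.
- **Small counts.** 432 against 420 is probably 26.25 rounded up, and 7.5 per club can be met with 7 or 8. Neither affects inference, but the paragraph should state one number.

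**Conclusion.** Wrong as written; it should be fixed, but it does not threaten the design. Under the article's own inputs, with the ±20 read as an SD and a two-sided test assumed, the clustered requirement uses up the 420 before any loss. After the assumed 20% loss, the unadjusted ferritin comparison has about 75% power by normal approximation, or 73% with t on 30 df, for 5 μg/L. The difference detectable with 80% power is then about 5.3 μg/L (2.80 × 20 × √(2/224)). Whether the planned adjusted analysis recovers 80% depends on a correlation that is not given. The counts of 432 and 420 per arm conflict. The cognitive allowance leaves 60 completers, 20 short of the stated 80, and the 80 does not follow from 0.7 SD, if that is the meaning of the 70%. The cognitive shortfall is one of headcount and justification, not a demonstrated loss of power.

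**What to change.** Rewrite the sample-size paragraph without enrolling more girls.

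1. Give one consistent number per club, per arm and in total: either 27 per club with 432 and 1296, or 26–27 per club summing to 420 and 1260.
2. State sidedness, and give ferritin power after 20% loss as about 73–75% for 5 μg/L. Alternatively, base the calculation on the planned baseline-adjusted mixed model and state the assumed baseline–endline correlation; an assumed r = 0.4 gives about 80–82% with 336 per arm.
3. For cognition, state 60 expected completers per arm after 50% loss, the effect size in SD units, and the power that follows.

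The cost is a rewording. The stated ferritin power becomes slightly less favourable, or comes to rest on an explicit correlation. Enrolment, conduct and analysis do not change.
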